### Statistical analysis plan

The full analysis set should be as close as possible to the intention-to-treat set. The direct deletion method will be used to treat missing data.

Continuous variables will be summarized as means with standard deviation and compared with *t*-tests or Wilcoxon rank-sum tests. Categorical variables will be expressed as percentages using the *χ*^2^ test or the Fisher exact test. Differences in diagnostic yield between the two techniques will be evaluated with the chi-squared test. Statistical significance will be considered for *P* < 0.05. All statistical analyses will be performed using SPSS (version 25.0, IBM, Armonk, NY).

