**Fig. 1 Fig1:**
[figure not shown]
CONSORT flowchart. Asterisk (*) symbol indicates the following: we will follow-up with all patients for postoperative complications after the procedure within 24 h and 72 h. If the pathologic diagnosis of EUS-FNB samples is obtained during the punctures, we will observe at follow-up 1 year later

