### Outcomes

The primary outcome is to compare the rate of diagnostic accuracy of EUS-FNB using the two different suction techniques (dry suction and wet suction). The rate will be calculated as the sum of true positive values and true negative values divided by the total number of samples, with an accurate diagnosis defined as a final diagnosis consistent with the tissue sample obtained during the needle passes.

The secondary outcomes include the optimal number of needle passes, sensitivity, specificity, specimen quality, cytological diagnoses, time of the procedure, and incidence of complications. Specificity analysis is only applicable to participants without malignancy, whereas sensitivity analysis is only applicable to persons with malignancy.

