### Final diagnosis

The malignant diagnosis was defined as the cytological or pathological diagnosis considered suspicious or positive for malignancy. Neuroendocrine tumors, solid pseudopapillary neoplasm, lymphoma, and melanoma were also considered to be malignant lesions.

The final diagnostic standards are as follows:For patients who undergo surgery, the final diagnosis will be based on the definite evidence of malignancy from surgical specimens.For patients who did not receive surgery, the final diagnosis will be considered as malignancy if cytologic or histologic diagnosis of malignancy is made by EUS-FNB with a corresponding clinical manifestation.For patients with negative or unsatisfactory pathological results, the final diagnosis will be confirmed by clinical and imaging follow-up for 1 year. If there was no imaging progression of the SPL, the true negative would be considered, and if there was progression or death, the false negative would be determined.

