### Sample size calculation

The sample size calculation was based on the primary outcome of diagnostic accuracy for the evaluation of solid pancreatic lesions. The reported diagnostic accuracy of EUS-FNB for SPL using dry suction is approximately 96.2%, and the wet suction technique is about 98.3% in the literature [6, 8]. Based on the reported data and the clinical judgment, the non-inferiority of dry suction in EUS-FNB will be assessed with a non-inferiority (*δ*) margin of 10%. With a two-sided test, a significance level of 2.5% (*α* = 0.025), and a power (1 − *β*) of 90%, using the PASS 15.0 software and a sample allocation ratio of 1:1 between the dry suction and wet suction groups, 180 patients should be enrolled. Considering a 10% dropout rate, a final sample of 200 participants (100 per group) is needed.

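### Direct deletion of missing outcomes falls almost entirely on negative or unsatisfactory biopsies, where nearly all inaccurate results sit, and is expected to favour non-inferiority

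*Protocol article*

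**What the plan says.** The Statistical analysis plan section gives one missing-data rule, with no exception for the primary endpoint: "The direct deletion method will be used to treat missing data". The sentence before it reads: "The full analysis set should be as close as possible to the intention-to-treat set".

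The primary outcome (Outcomes section) is "the sum of true positive values and true negative values divided by the total number of samples". Whether a result counts as true or false depends on the Final diagnosis section, which has three routes:

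- Operated patients are settled by the surgical specimen.
- For unoperated patients with a malignant biopsy, "the final diagnosis will be considered as malignancy if cytologic or histologic diagnosis of malignancy is made by EUS-FNB with a corresponding clinical manifestation".
- For the rest: "For patients with negative or unsatisfactory pathological results, the final diagnosis will be confirmed by clinical and imaging follow-up for 1 year". A lesion without imaging progression is then a true negative; "if there was progression or death, the false negative would be determined".

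The Sample size calculation allows for loss: "Considering a 10% dropout rate, a final sample of 200 participants (100 per group) is needed".

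**The concern.** Deletion is harmless when the chance of being missing has nothing to do with the outcome. Here the reference standard ties the two together. A malignant biopsy in an unoperated patient is settled by the biopsy and the clinical picture, without a year of follow-up. A negative or unsatisfactory biopsy stays unscored until that year is complete. Loss to follow-up therefore removes patients from the one group in which a false negative can occur.

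If dry suction is truly worse, the dry arm has more false negatives in that group. Equal loss rates then delete more failures from the dry arm than from the wet arm, and the observed gap narrows. In a superiority trial this would tend to be conservative. In a non-inferiority trial it raises the chance of accepting a technique that is worse by the full margin.

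**Working it through.** **The plan's own figure.** With 96.2% (dry), 98.3% (wet), a 10-point margin, one-sided 0.025 and 90% power: n per arm = (1.960 + 1.282)² × (0.962×0.038 + 0.983×0.017) / (0.100 − 0.021)² = 10.51 × 0.05327 / 0.006241 ≈ 89.7, so 90 per arm and 180 in all; 180/0.9 = 200. The stated sample size reproduces.

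**Inputs.** From the article: 100 per arm, the 10-point margin and the planning rates. Assumed, because the article does not give them: true accuracy at the margin of 88% v 98%, true negatives 12% of each arm, specificity 100%, the loss fractions, and the Newcombe 95% lower limit compared with −10 points as the decision rule.

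**Expected accuracy after deletion.** With L_T and L_F the fractions lost among true negatives (TN) and false negatives (FN), and TP the true positives:

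A = [TP + (1 − L_T)·TN] / [TP + (1 − L_T)·TN + (1 − L_F)·FN]

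Per 100 patients, dry has TP 76, TN 12, FN 12; wet has TP 86, TN 12, FN 2. Example with 20% loss of both kinds: dry = (76 + 9.6)/(76 + 9.6 + 9.6) = 85.6/95.2 = 89.9%; wet = (86 + 9.6)/(86 + 9.6 + 1.6) = 95.6/97.2 = 98.4%. The gap is 8.4 points instead of 10.

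**False non-inferiority** (200,000 simulated trials per row):

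| Loss of FN / TN | Missing, dry / wet | Expected gap (points) | Deletion | Missing counted as inaccurate |
|---|---|---|---|---|
| 0 / 0 | 0 / 0 | 10.0 | 2.1% | 2.1% |
| 10% / 10% | 2.4% / 1.4% | 9.2 | 3.4% | 2.2% |
| 20% / 20% | 4.8% / 2.8% | 8.4 | 5.3% | 2.3% |
| 40% / 40% | 9.6% / 5.6% | 6.7 | 13% | 2.4% |
| 60% / 30% | 10.8% / 4.8% | 4.5 | 37% | 2.3% |
| 10% / 30% | 4.8% / 3.8% | 9.5 | 2.9% | 2.3% |
| 0 / 30% | 3.6% / 3.6% | 10.4 | 1.7% | 2.4% |

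**Other assumptions.** With 88.3% v 98.3%, 85% malignancy and equal loss of 10%, 25% and 50% among negatives, the Newcombe error goes from 2.1% to 3.3%, 6.4% and 19.7%. With a Wald limit it goes from 3.8% to 6.7%, 13.5% and 37%. Results at 80% and 90% malignancy are similar.

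**Power at the planning rates** (96.2% v 98.3%, 12% true negatives, Newcombe, 100 per arm). Without loss it is 77%; this is below the planned 90% because the Newcombe limit is wider than the normal approximation at such high proportions, not because of missing data. With 10%, 20% and 40% loss among negatives, counting missing as inaccurate gives 68%, 61% and 50%. Deletion gives 79%, 82% and 89%; that apparent gain is the same bias, since the expected gap falls from 2.1 to 1.35 points at 40% loss.

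**The case against.** A reader might infer that deletion simply removes the failures, so that bias toward non-inferiority is certain. The article does not support that. The deletable group also holds the unoperated true negatives, which count as accurate. At the planning rates with 12% true negatives they are 12/15.8 = 76% of that group in the dry arm and 12/13.7 = 88% in the wet arm, so with equal loss most deleted patients would be accurate results. Accuracy still rises, because 76% is below the arm's 96.2% and 88% is below 98.3%. The direction is therefore the expected one under similar loss, not a certainty.

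The loss pattern could also run the other way. A known death or progression is scored, and surgery settles the diagnosis, so missed cancers have more ways of being resolved than stable benign lesions. This stands, and it is why the 37% row should not be the headline: nothing in the article suggests that false negatives are lost twice as often as true negatives. Full reversal, however, needs a strong imbalance. With 10% loss of false negatives, true negatives must be lost about 4.3, 5.8 or 8.7 times as often at 80%, 85% or 90% malignancy. Clearly heavier loss in the wet arm would also offset the bias.

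The article promises telephone contact and pays participants who complete follow-up, and nothing says that the 10% dropout falls on biopsy-negative patients. Both points bear on size: at 10% equal loss the error is only 3.4%.

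A reader might also say that deletion flatly contradicts intention-to-treat. The wording "The full analysis set should be as close as possible to the intention-to-treat set" leaves room for exclusions, so the two sentences are in tension rather than contradiction.

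Finally, the Fig. 1 note says "If the pathologic diagnosis of EUS-FNB samples is obtained during the punctures, we will observe at follow-up 1 year later", which might suggest that positives can be lost too. The Final diagnosis section does not need that visit to score a positive. Withdrawal before biopsy can also produce missing data, but it is not tied to the biopsy result.

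**Conclusion.** The concern holds. The article states the deletion rule outright, so this is not a detail left to a fuller document. Combined with the reference standard, the rule concentrates deletion of the primary outcome in the group that contains practically all inaccurate results. With similar loss by arm, and dry truly 10 points worse, false non-inferiority goes from 2.1% to about 3.4%, 5.3% and 13% at 10%, 20% and 40% loss among negatives. Even the last case leaves under 10% of each arm missing, so total missingness within the dropout allowance gives no reassurance.

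The size rests on assumed accuracy, prevalence, loss rates and interval method. With 10% of false and 30% of true negatives lost, the error is 2.9%; with 0% and 30%, it is 1.7%, which is conservative. None of this makes deletion a sound sole rule for the primary endpoint.

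**What to change.** Replace direct deletion for the primary endpoint:

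- Include in the primary analysis all randomised patients who undergo EUS-FNB, in the arm assigned.
- Handle an unestablished final diagnosis by one prespecified method that does not drop the patient. Either count it as not accurate in both arms, or use multiple imputation conditional on biopsy result, arm and baseline data. The imputation assumes that, given those variables, loss does not depend on the true diagnosis.
- Report the missing-as-inaccurate, tipping-point and complete-case results alongside, and require the non-inferiority conclusion to be robust to them.
- Report missing final diagnoses by arm and biopsy result.

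The cost is some analysis work and slightly lower reported accuracy in both arms if missing is counted as inaccurate. That option also lowers power, from about 77% to 68%, 61% and 50% with 10%, 20% and 40% loss among negatives at the planning rates. The plan should state this figure when it chooses the method, and the sample size should be rechecked against it. With 123 of 200 patients enrolled at the date given under Trial status, an amendment before the data are analysed was still feasible.

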**Discussion:**

This study has been designed to determine (i) whether EUS-FNB using 22G Franseen needle with dry suction is non-inferior to wet suction in terms of diagnostic accuracy and (ii) the optimal number of passes during EUS-FNB of SPLs using 22G Franseen needle.

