### Specimen

After 3 needle passes, the doctor will evaluate the adequacy of the sample with macroscopic on-site evaluation (MOSE) and decide whether to continue additional punctures. MOSE was performed by gross visualization of the collected material by the endoscopists and considered adequate when a white/yellowish aggregate core longer than 10 mm was retrieved. Three needle passes at least were required for both groups. The specimens obtained at each pass will be marked and sent to pathology separately. It is to be evaluated using traditional cytological smear, liquid-based thin layer cytological examination, and histological examination for each pass.

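### The tests named for categorical outcomes assume independent groups, so they do not suit the within-patient comparison of accuracy after 1, 2 and 3 passes that the second aim requires

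*Protocol article*

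**What the plan says.** The Abstract (Discussion paragraph) names two purposes. The second is to determine "the optimal number of passes during EUS-FNB of SPLs using 22G Franseen needle". The Outcomes section repeats it among the secondary outcomes: "The secondary outcomes include the optimal number of needle passes".

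The Specimen section fixes how the data arise. "Three needle passes at least were required for both groups", and "The specimens obtained at each pass will be marked and sent to pathology separately". After the third pass the endoscopist judges the material by macroscopic on-site evaluation (MOSE), with a sample "considered adequate when a white/yellowish aggregate core longer than 10 mm was retrieved". The endoscopist will then "decide whether to continue additional punctures".

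The Statistical analysis plan section covers continuous variables with the t-test or Wilcoxon rank-sum test. For the rest, "Categorical variables will be expressed as percentages using the" chi-squared or Fisher exact test. The one comparison it names is diagnostic yield between the two techniques, by chi-squared. It makes no exception for data on successive passes.

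**The concern.** The pass-number aim is a question within patients: how many more patients are correctly diagnosed once a second or third pass is added to what they already had. Every patient contributes to each of passes 1 to 3, so the proportions being compared come from the same people and are correlated. A test for two independent groups ignores that correlation and, when it is positive, overstates the standard error of the gain.

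The direction matters. An interval that is too wide makes a real gain from a further pass easier to read as no difference, and so supports stopping earlier. The main Discussion says that fewer passes benefit patients and expects that limited passes may be enough, so the error leans towards the conclusion the trial anticipates.

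A second, smaller point concerns passes beyond three. They exist only where the operator chose to go on, so those patients are a selected subset and not comparable with the full set at passes 1 to 3.

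**Working it through.** **The plan's own figure.** The article gives no figure for the pass-number aim. Its only calculation is for the primary comparison (Sample size calculation section: 98.3% wet, 96.2% dry, margin 10 points, alpha 0.025, power 90%). With 0.025 in one tail and unpooled variance:

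n per arm = (1.960 + 1.282)² × (0.983×0.017 + 0.962×0.038) / (0.10 − 0.021)² = 10.51 × 0.05327 / 0.006241 ≈ 89.7, so 90 per arm, 180 in all, and 180/0.9 = 200.

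The stated 180 and 200 reproduce. Nothing below changes them.

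**Inputs for the pass comparison.** From the documents: 200 patients, at least three passes each, each pass read separately. Assumed, because the documents give no accuracy by pass and no within-patient correlation: 184/200 cumulatively correct after two passes and 190/200 after three, with 6 patients gained and 0 lost.

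**Unpaired interval.** This matches the independent-groups assumption of the named tests.
- SE = √(0.92×0.08/200 + 0.95×0.05/200) = √0.0006055 = 0.0246
- 95% CI = 3.0 ± 1.96×2.46 = **-1.8 to 7.8 points**

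**Paired interval.** With b gained and c lost among n patients, SE = √[(b + c) − (b − c)²/n] / n.
- SE = √(6 − 36/200) / 200 = 2.412/200 = 0.0121
- 95% CI = 3.0 ± 1.96×1.21 = **0.6 to 5.4 points**

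The unpaired interval is 0.0246/0.0121 ≈ 2.0 times as wide.

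**What the unpaired formula assumes.** If results after two and three passes were independent, the expected gains would be 200×0.08×0.95 = 15.2 and the expected losses 200×0.92×0.05 = 9.2. Putting these into the paired formula gives √(24.4 − 0.18)/200 = 0.0246, the unpaired SE. So the unpaired interval behaves as if about nine patients lost a correct diagnosis through a further pass.

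**Range over the assumed counts (Wald intervals, same formulas).**

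| Patients | Correct before → after | Gained / lost | Unpaired 95% CI | Paired 95% CI |
|---|---|---|---|---|
| 200 | 184 → 190 | 6 / 0 | -1.8 to 7.8 | 0.6 to 5.4 |
| 200 | 184 → 190 | 7 / 1 | -1.8 to 7.8 | 0.3 to 5.7 |
| 200 | 184 → 190 | 9 / 3 | -1.8 to 7.8 | -0.4 to 6.4 |
| 100 | 90 → 95 | 5 / 0 | -2.3 to 12.3 | 0.7 to 9.3 |
| 100 | 85 → 92 | 7 / 0 | -1.8 to 15.8 | 2.0 to 12.0 |

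The paired interval is narrower in every row. Whether it excludes zero depends on the number lost.

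**Error rate.** A simulation (20,000 runs, 100 patients, assumed accuracy 85% at each single pass) tested pass 1 against pass 2 in the same patients as if they were independent groups. The true type I error was about 3.8%, 2.1% and 0.7% at within-patient correlations of 0.1, 0.3 and 0.5, against a nominal 5%. The test is conservative, increasingly so as the correlation rises.

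**The case against.** The strongest reply is that the Statistical analysis plan section never assigns a test to the pass-number outcome. In a two-arm parallel trial its general sentences are naturally read as dry versus wet, and for that use they are sound: accuracy at a given pass from 1 to 3, or a rank-sum test on passes per patient. A fuller plan could name a paired method. The absence of a definition of the optimal number is likewise a detail an article may leave to that plan, and it is not criticised here.

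Most of this stands, and it limits the point. It does not remove it. Between-arm tests cannot answer a within-patient aim, and the only tests the section states, under a rule without exceptions, are unsuitable for that aim.

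Five stronger readings are tempting but unsupported:

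- **That the article commits to testing pass 2 against pass 3 by chi-squared.** It does not say so. The tests reach this outcome only through the general rule.
- **That raw accuracy at passes 4 and later will be compared with earlier passes.** No such comparison is proposed.
- **That extra passes occur only when MOSE is inadequate.** That is a likely pattern. The Specimen section states only an operator decision after MOSE.
- **That P-values prove the case.** For the 6 / 0 example chi-squared gives 0.22 and exact McNemar 0.03. If losses are impossible, though, a single gain already refutes McNemar's null, so the contrast says little. The intervals are the useful comparison. Nor do the documents rule out losses: under Final diagnosis a suspicious result counts as malignant, so a later pass could overturn a true negative.
- **That the primary result is affected.** It is a between-arm comparison, and this point does not touch it.

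**Conclusion.** The point holds in limited form. If the stated rule for categorical outcomes is applied to accuracy after 1, 2 and 3 passes in the same patients, the standard error is wrong and, with positive correlation, too large. In the main illustration the interval for a 3-point gain is about twice as wide as it should be and includes zero where the paired interval does not.

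The size rests on assumed counts. The direction rests only on positive within-patient correlation, which is close to certain for cumulative results because each includes the one before. With as many as 3 losses among 200 the paired interval also includes zero, though it is still narrower.

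The outcome is secondary but is one of two stated aims, so the change should be made. Confidence is medium, because a fuller analysis plan may already cover it.

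**What to change.** In the Statistical analysis plan section:

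1. State that the chi-squared and Fisher tests apply to comparisons between the dry and wet arms.
2. For the pass-number aim, take the patient as the unit and analyse cumulative diagnostic accuracy after passes 1, 2 and 3. Report paired differences between successive passes with 95% CIs, by a method that suits few discordant pairs, or use a GEE clustered by patient. Give results by arm and pooled.
3. Report passes beyond three descriptively, with the number of patients who had them, because they follow the operator's decision after MOSE.

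The cost is wording and a little more analysis work. No new data are needed, since specimens are already labelled and sent to pathology by pass. At the article's status date (13 October 2023) 123 patients had been enrolled, and patients with negative or unsatisfactory pathology need one year of follow-up, so there was time to make the change before the final analysis. The sample size stays at 200.

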## Methods

### Study design

This is a multicenter, open-label, randomized controlled non-inferiority trial with two parallel groups. Two hundred patients with SPLs will undergo EUS-FNB using 22G Franseen needles in 4 tertiary Chinese hospitals and will be randomly assigned to the dry suction group and the wet suction group in a ratio of 1:1. A checklist with the recommendations for Interventional Trials (SPIRIT) is attached as Additional file 1. Study flowchart and standard protocol items displaying the trial’s enrollment, intervention, and assessment schedules were showed in Figs. 1 and 2, respectively.

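### The trial is sized for non-inferiority with a 10-point margin, but the only between-group tests stated for a binary outcome are tests of difference that never use the margin

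*Protocol article*

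**What the plan says.** - **Design and question.** Study design states: "This is a multicenter, open-label, randomized controlled non-inferiority trial with two parallel groups". The Discussion paragraph of the Abstract asks whether dry suction "is non-inferior to wet suction in terms of diagnostic accuracy".
- **Primary endpoint.** Outcomes: "The primary outcome is to compare the rate of diagnostic accuracy of EUS-FNB using the two different suction techniques". It is a binary endpoint.
- **Sizing.** Sample size calculation says "the non-inferiority of dry suction in EUS-FNB will be assessed" with a margin of 10%. The inputs are: "The reported diagnostic accuracy of EUS-FNB for SPL using dry suction is approximately 96.2" per cent, and "the wet suction technique is about 98.3% in the literature". With a significance level of 2.5% and 90% power it arrives at 180 patients, raised to 200 for 10% dropout.
- **Analysis.** The Statistical analysis plan section assigns chi-squared or Fisher tests to categorical variables in general. It then adds: "Differences in diagnostic yield between the two techniques will be evaluated with the chi-squared test". The significance threshold is P < 0.05. The section mentions no margin, no confidence interval for the difference and no rule for concluding non-inferiority, and neither does any other section.

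**The concern.** The sizing and the analysis address different hypotheses. The sizing tests H0: dry minus wet ≤ -10 points. The chi-squared and Fisher tests address H0: dry minus wet = 0. A non-significant test of difference does not show that dry is within 10 points of wet, and a significant one does not show that it is outside.

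At the planning rates a non-significant result is also by far the likeliest outcome. With no decision rule in the analysis section, such a result could easily be reported as dry being as good as wet, and nothing in the plan limits the error of that reading to 2.5%.

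**Working it through.** **Inputs (Sample size calculation).** Dry 96.2%, wet 98.3%, margin 10 points, significance level 0.025, power 90%, 1:1 allocation, 10% dropout.

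**1. Reproduce the plan's figure.** Unpooled normal formula, one-sided 0.025:

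n per arm = [p_d(1-p_d) + p_w(1-p_w)] × (z_0.975 + z_0.90)² / [margin - (p_w - p_d)]²

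= [0.962×0.038 + 0.983×0.017] × (1.960 + 1.282)² / (0.10 - 0.021)²

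= 0.053267 × 10.507 / 0.006241 = 89.7, rounded up to 90.

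Two arms give 180, and 180/0.90 = 200. The plan's figures are reproduced, so the sample size is a margin-based calculation. (The section words the 2.5% test as two-sided. Taken literally, 0.0125 per side, the formula gives 106 per arm, or 212. Only one-sided 0.025 gives 180, and it is used below.)

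**2. What the stated test does at those rates.** I enumerated all pairs of binomial outcomes and summed the probability that the uncorrected Pearson chi-squared gives P < 0.05. At 96.2% v 98.3% this is 12% at 90 per arm and 13% at 100 per arm. A non-significant result is therefore expected in about 87-88% of trials.

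**3. Error if P ≥ 0.05 were read as non-inferior.** The same enumeration, with dry truly 10 points worse:

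| True dry v wet | n per arm | chi-squared P ≥ 0.05 | Fisher P ≥ 0.05 | Newcombe lower limit above -10 |
|---|---|---|---|---|
| 88.3% v 98.3% | 90 | 19% | 28% | 2.2% |
| 88.3% v 98.3% | 100 | 14% | 22% | 2.1% |
| 85% v 95% (assumed) | 90 | 37% | 45% | 2.4% |

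The first two rows take the plan's wet rate and subtract the margin. The rates in the third row are an assumption, included to show how the error grows when accuracy is lower than planned.

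**4. Single results on which the two analyses disagree (illustrative counts).**

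- *92/100 dry v 98/100 wet.* Chi-squared: pooled rate 0.95, z = 0.06/√(0.95×0.05×2/100) = 1.947, P = 0.052, not significant. Newcombe: Wilson lower limit for dry 0.850, Wilson upper limit for wet 0.9945; lower limit = -0.06 - √[(0.92-0.850)² + (0.9945-0.98)²] = -13.1 points. Non-inferiority is not shown.
- *96/100 dry v 100/100 wet.* Chi-squared: pooled rate 0.98, z = 0.04/√(0.98×0.02×2/100) = 2.020, P = 0.043, significant. Newcombe: Wilson lower limit for dry 0.9016; lower limit = -0.04 - (0.96-0.9016) = -9.8 points. Non-inferiority is shown.

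The second kind of disagreement is rare. At the planning rates, with Newcombe, its probability is 0.2% at 90 per arm and 3.8% at 100 per arm. The first kind (not significant, non-inferiority not shown) has probability 15% and 14%.

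**5. Power of a margin-based analysis at the planning rates.** By normal approximation the unpooled Wald version has 90.1% at 90 per arm and 92.8% at 100 per arm. By exact enumeration a Newcombe 95% interval has 73% and 77%.

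**The case against.** **A full SAP may exist and supply the margin test.** Silence in a journal article could be excused on that ground. Here, though, the article does state the between-technique test and its threshold, and they do not fit its own hypothesis.

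**The intention to use the margin is documented.** This stands, and it limits the point. Sample size calculation says non-inferiority will be assessed with the 10% margin. A reader might infer that the plan means to declare non-inferiority from P ≥ 0.05. The documents do not say so. The error rates above are conditional on that reading, and the defect is that the analysis section contains nothing that uses the margin.

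**The chi-squared sentence is about diagnostic yield, not accuracy.** The term is a keyword and recurs in the Discussion, so it may be loose wording for accuracy. A reader might infer that the primary endpoint has been switched; the text does not support that. If the sentence means accuracy, the test does not fit. If yield is a separate measure, accuracy falls under the general categorical-variables sentence, which prescribes the same kind of test. The point holds either way.

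**A significant chi-squared test for a small gap proves a conflict.** Not always. For 86/90 dry v 90/90 wet, chi-squared gives P = 0.043 for a 4.4-point gap, but the Newcombe lower limit is -10.9 points, so non-inferiority is not shown either and the analyses do not conflict. With so few failures Fisher would be the natural choice, and it gives P = 0.12. The practical risk lies almost wholly in misreading a non-significant result.

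**Conclusion.** The point holds. The article sets a non-inferiority question with a 10-point margin and sizes the trial on it, yet the tests it states for a binary outcome are tests of difference at P < 0.05. As the analysis section stands, the primary question has no test that matches it.

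If non-significance were taken as non-inferiority, the error at the margin would be 14-19% by chi-squared and 22-28% by Fisher at the plan's wet rate, against 2.5%. It would be higher if true accuracy is lower than planned. These figures assume independent binomial outcomes per patient, 90 or 100 per arm, and that reading of the P value.

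The sample size is not shown to be miscalculated: 180 follows from the unpooled normal formula at one-sided 0.025. A reader might also infer that correcting the analysis is only a change of wording. It is not, because a Newcombe interval does not deliver the stated 90% power at the planning rates.

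**What to change.** In the Statistical analysis plan section, replace the chi-squared sentence with a primary analysis along these lines:

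> The primary analysis is the difference in per-patient diagnostic accuracy, dry minus wet, with a two-sided 95% confidence interval by the [named] method. Non-inferiority is concluded if the lower limit is above -10 percentage points.

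- Name the interval method before analysis. Newcombe and Miettinen-Nurminen are examples; any margin-based method fixed in advance would cure the mismatch.
- Keep chi-squared and Fisher tests for baseline and secondary comparisons.
- Replace *diagnostic yield* with *diagnostic accuracy*, so that the sentence matches the Outcomes section.
- State in Sample size calculation that the 2.5% is one-sided, which is what 180 rests on and what a two-sided 95% interval implements.

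**Cost.** No new data items are needed. Power has to be restated for the chosen method: with Newcombe, about 73% at 90 per arm and 77% at 100 per arm, against the stated 90%. The sponsor must either accept and disclose this or revisit the sample size. At the article's status date (October 13, 2023) 123 of 200 patients had been enrolled, so at that point the change could still be made before the analysis.
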